## Design of the study

The ARES study consists of two sequential parts, “A” and “B” (Fig. 1). Three-hundred ET eligible patients, after signing an informed consent, will start a run-in phase, whereby they will be instructed to take their aspirin tablet at breakfast (7–9 a.m.) for 7–10 consecutive days, thus allowing synchronizing aspirin intake. Upon run-in completion, patients will enter study part A.

**Fig. 1 Fig1:**
[figure not shown]
Trial design. The flow chart depicts the design and phases of the ARES study

### Part A

Patients will be randomized (1:1:1) in a double-blind fashion to aspirin 100 mg od (standard of care), 100 mg bid (i.e. breakfast and dinner), or 100 mg tid (i.e., breakfast, lunch, and dinner). Matching placebo will be used so that all patients will take active drug and placebo tablets tid. At randomization and after 2 weeks of study treatment, patients will undergo blood and urine sampling for serum TXB_2_ and urinary PGIM and TXM measurements at 8 a.m., immediately before aspirin dosing; thereafter, they will resume their open-label, standard aspirin regimen for the time interval necessary to assay serum and urine samples and analyze the data. The primary end points of part A will assess the biochemical efficacy, as reflected by the degree of suppression of serum TXB_2_ throughout the dosing interval, and biochemical safety, as assessed by urinary PGIM excretion, of the two experimental dosing regimens as compared to the standard regimen of aspirin administration. The secondary end point will assess their impact on in vivo platelet activation, as reflected by the urinary excretion of TXM.

### Part B

The experimental aspirin regimen associated with a significantly lower serum TXB_2_ level and non-inferior urinary PGIM excretion rate (i.e., ≤30% reduction) as compared to aspirin 100 mg od, will be selected for part B, and patients will be randomized in an open-label fashion to the standard vs. the optimized multiple dosing regimen for 20 months. The primary end point of part B will assess the long-term persistence of the superior biochemical efficacy of the optimized vs. standard aspirin regimen, in at least 6 out of 10 determinations of serum TXB_2_ that will be performed over 20 months. Secondary end points of part B will explore the following: (i) the safety of the experimental aspirin regimen, as reflected by any major bleeding and gastrointestinal symptoms considered attributable to aspirin; (ii) effectiveness in reducing MPN-specific symptom burden and pain attributable to microcirculatory disturbances; and (iii) stability over 20 months of the degree of platelet activation in vivo, as assessed by urinary TXM. The stability of TXM will be assessed in a subgroup of 150 patients.

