## Study objectives

The ARES study has two primary objectives:To investigate whether aspirin regimens based on bid or three times daily (tid) administration of 100 mg result in a more complete suppression of platelet-derived TXA_2_ throughout the dosing interval, without significantly affecting in vivo PGI_2_ biosynthesis, as compared to the standard od regimen. Serum TXB_2_ will be measured as an index of platelet COX-1 activity, specifically reflecting the antiplatelet pharmacodynamics of aspirin (biochemical efficacy) (http://www.ema.europa.eu/docs/en_GB/document_library/Scientific_guideline/2009/09/WC500003340.pdf). A major urinary PGI_2_ metabolite, 2,3-dinor-6-keto-PGF_1alfa_ (PGIM) will be measured to assess the impact of different aspirin regimens on vascular COX-2 activity (biochemical safety)^32^. The comparison between aspirin 100 mg bid or tid vs. 100 mg od will test a superiority hypothesis in terms of serum TXB_2_ levels associated with each experimental vs. standard regimens. PGIM comparisons will assess the non-inferiority of any multiple daily dosing regimen vs. the standard od regimen. This objective will be addressed by a randomized, parallel-arm, double-blind, controlled study of 2-week aspirin treatment (part A) aimed at identifying the aspirin regimen to be further evaluated during long-term follow-up in the second part (part B) of the study.To evaluate the long-term persistence of superior biochemical efficacy of an optimized, multiple daily dosing regimen, as compared to the aspirin 100 mg od regimen. Biochemical efficacy will be assessed by repeated measurements of serum TXB_2_ (every 3 months over 20 months). A multiple daily dosing regimen will be tested for superiority vs. od dosing in terms of biochemical efficacy throughout the dosing interval, in an open-label, randomized study comparing aspirin 100 mg od vs. the optimal multiple daily dosing regimen identified in part A, with a follow-up of 20 months. This long-term follow-up will also provide an estimate of compliance with the experimental dosing regimen.

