The secondary exploratory objectives will be:To assess the safety of the multiple daily aspirin regimen by recording: major bleeding and clinically relevant non-major bleeding events defined according to the Scientific and Standardization Committee of the International Society on Thrombosis and Haemostasis^34,35^, as well as any upper gastrointestinal non-bleeding adverse events, which may be considered attributable to aspirin (e.g., ulcer or perforation > grade 2).To record any thrombotic complication, as previously defined^3^. Briefly, major arterial thrombosis will include the following: acute coronary syndrome; any ischemic stroke (major and minor); and peripheral arterial thrombosis, including thrombotic digital ischemia and retinal arterial thrombosis. Major venous thrombosis will include thrombosis in the following districts: deep veins of the limb and/or abdomen; cerebral and splanchnic veins; retinal vein, as well as pulmonary embolism. Splanchnic venous thrombosis will include hepatic, portal, mesenteric, and splenic veins. Transient ischemic attack and superficial vein thrombosis of the limbs will be considered as minor thrombosis.To assess the tolerability of the experimental dosing regimen by recording the gastrointestinal symptoms by the severity of dyspepsia assessment questionnaire^36^.To evaluate the potential benefit of multiple doses of aspirin on the MPN-related symptom burden by a questionnaire aimed to capture all microvascular symptoms^37^, including the MPN Symptom Assessment and a pain numeric rating scale for erythromelalgia.To assess the stability over time of in vivo platelet activation, as assessed by urinary TXM excretion, in a subset of patients, in a non-invasive substudy.To assess whether the pre-fibrotic/early primary myelofibrosis (pre-PMF) phenotype now distinguished in the revised 2016 WHO classification^38^ has a higher incidence in the patients who will develop major or clinically relevant non-major bleeding during follow-up.

These secondary assessments will be performed in part B of the study, over 20-month treatment.

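### In open-label Part B, the gastrointestinal safety count depends on attribution to aspirin, so knowing the regimen can inflate or hide a between-arm difference

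*Protocol article*

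**What the plan says.** All points are in the protocol article.

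- **Blinding.** Under Part B, "patients will be randomized in an open-label fashion to the standard vs. the optimized multiple dosing regimen for 20 months". The Study objectives section says the same: "in an open-label, randomized study comparing aspirin 100 mg od vs. the optimal multiple daily dosing regimen identified in part A". It also places all the secondary assessments, safety included, in Part B.
- **Safety end point, Part B section.** Safety is assessed "as reflected by any major bleeding and gastrointestinal symptoms considered attributable to aspirin".
- **Safety objective, Study objectives section.** The non-bleeding component is "any upper gastrointestinal non-bleeding adverse events, which may be considered attributable to aspirin", with ulcer or perforation above grade 2 given as the example. The bleeding component is "major bleeding and clinically relevant non-major bleeding events defined according to the Scientific and Standardization Committee" of the International Society on Thrombosis and Haemostasis, with no attribution condition.
- **Tolerability, Study objectives section.** This is a separate item: "recording the gastrointestinal symptoms by the severity of dyspepsia assessment questionnaire". It carries no attribution condition.
- **Status.** The objectives, the Part B section and the section on end points and statistical analysis all describe the safety assessment as secondary and exploratory. No event rate, test, margin or power is stated for it.
- **Blinded review in Part B.** The only one described is the pathologists' re-reading of bone marrow biopsies, in the section on end points and statistical analysis.

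**The concern.** Both arms take 100 mg aspirin tablets and differ only in the number of daily doses. A rule that counts a gastrointestinal event only when it is attributed to aspirin puts a causality judgement between the event and the analysis. If the person judging knows the regimen, the same ulcer may be attributed more readily in a patient on two or three doses a day than in a patient on one. Someone who favours the new regimen may lean the other way. Either way, the probability of being counted can differ by arm although randomisation has made the arms comparable.

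The abstract's second question is whether superior biochemical efficacy can be maintained safely, and the Conclusions section says the preliminary tolerability and safety assessment will inform the phase III design. An arm-dependent filter could pass on a gastrointestinal signal that is not there, or fail to pass on one that is.

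A smaller, separate matter is that the bleeding component is worded differently in different sections.

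**Working it through.** **No figure to reproduce.** The article gives no rate or power for this end point. What follows sets the texts side by side and then illustrates the size with assumed rates.

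**Step 1: where the filter applies.**

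| Component | Study objectives | Part B section | Attribution filter |
|---|---|---|---|
| Gastrointestinal events | Upper, non-bleeding; example of type and grade | Gastrointestinal symptoms | In both |
| Bleeding | Major plus clinically relevant non-major | Major only | None in the objectives; not clearly any in the Part B section |
| Dyspepsia questionnaire | Separate tolerability measure | Not named | None |

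The pre-specified comparison of bleeders with non-bleeders for pre-fibrotic myelofibrosis, in the statistical section, uses both bleeding categories. It therefore agrees with the objectives and not with the shorter Part B wording.

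**Step 2: form of the bias.** Let p be the true event risk and a the probability that an event is called attributable. Then

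counted risk = p × a, and counted ratio = (p_multiple / p_od) × (a_multiple / a_od).

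The second factor is the distortion. It equals 1 only when attribution is equally likely in both arms.

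**Step 3: illustration.** Inputs:

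- 300 patients in Part B (statistical section), taken as 300 / 2 = 150 per arm. The 1:1 ratio and absence of dropout are assumptions.
- Two-sided test at 0.05 (assumed).
- All event risks and attribution probabilities (assumed).

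The chance of a nominally significant difference is Φ[(|d| − 1.96 × SE0) / SE1], where d is the difference in counted risks, SE0 is the pooled and SE1 the unpooled standard error.

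| True risk, od / multiple | Attribution, od / multiple | Counted risk | Ratio | Chance of significance |
|---|---|---|---|---|
| 10% / 10% | 50% / 80% | 5% / 8% | 1.6 | 0.18 |
| 10% / 10% | 50% / 70% | 5% / 7% | 1.4 | 0.11 |
| 20% / 20% | 50% / 70% | 10% / 14% | 1.4 | 0.19 |
| 30% / 30% | 50% / 70% | 15% / 21% | 1.4 | 0.27 |
| 10% / 10% | 40% / 80% | 4% / 8% | 2.0 | 0.31 |
| 20% / 20% | 40% / 80% | 8% / 16% | 2.0 | 0.57 |
| 30% / 30% | 40% / 80% | 12% / 24% | 2.0 | 0.78 |
| 20% / 35% | 80% / 50% | 16% / 17.5% | 1.09 | 0.05 |
| 20% / 35% | 50% / 50% | 10% / 17.5% | 1.75 | 0.47 |
| 20% / 35% | all counted | 20% / 35% | 1.75 | 0.83 |

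A milder split of 50% against 65% at a true 10% gives 5.0% against 6.5%, ratio 1.3. In patients, the first row is 150 × 0.05 = 7.5 against 150 × 0.08 = 12 events.

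**Step 4: reading the table.** With equal true risks, where the error rate should be 0.05, the first seven rows run from 0.11 to 0.78. In the eighth row a true ratio of 1.75 is counted as 1.09. Equal attribution in both arms leaves the ratio intact but loses events. With all events counted, and reporting equally complete in both arms, the ratio is the true one.

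**The case against.** Several points on the other side have force.

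- **Who judges is not stated.** The article does not say who attributes events or whether they know the arm. The full protocol is not shown and may provide blinded adjudication, so judgement with the regimen known is an inference from the open-label design. This stands as a limit on certainty.
- **Another reading of the objectives.** The phrase about what may be considered attributable, followed by an example of type and grade, could describe a class of aspirin-type events and not a case-by-case judgement. That is tenable for the objectives. The Part B wording reads more naturally as a filter on individual events, although it is a one-line summary.
- **Some data carry no filter.** The dyspepsia questionnaire records symptoms without attribution, and bleeding follows a published definition. A reader might infer that the whole safety end point is distorted; the documents do not support that. The questionnaire is still answered by patients who know their regimen, and it does not cover ulcer or perforation.
- **The filter has a purpose.** A reader might conclude that it adds only bias. It can also remove background events unrelated to aspirin, so the choice trades specificity against bias.
- **Low stakes for the main result.** The end point is exploratory, has no stated test, and plays no part in choosing the regimen or in the primary serum TXB2 comparison. This stands.
- **The bleeding mismatch looks like shorthand.** A reader might infer two rival bleeding end points. The objectives give the full definition, and the statistical section refers back to details given earlier and uses both categories. The Part B sentence is more likely an abbreviated restatement.

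**Conclusion.** The point holds for the gastrointestinal component of the secondary, exploratory safety end point. As worded, its count depends on attribution to aspirin in an open-label comparison where both arms take aspirin, and the article describes no blinding of that judgement. The direction of any distortion cannot be known in advance.

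Its size cannot be derived from the article. Under the assumed rates, spurious ratios run from 1.3 to 2.0, and a true ratio of 1.75 can shrink to 1.09. These figures show what the wording permits; they do not predict what will occur.

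It would go too far to say that the safety results as a whole are unreliable, or that dropping the filter makes the comparison unbiased: patients and sites would still report and grade complaints knowing the regimen. The bleeding wording is a minor inconsistency to tidy up. What is affected is the gastrointestinal safety information passed to phase III.

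**What to change.** 1. **Main gastrointestinal safety analysis.** In the Study objectives and Part B sections, define it as the comparison by randomised arm of all upper gastrointestinal adverse events of the stated type and grade, regardless of attribution. The type and grade now appear only as an example, so they should be written as the definition and used identically in both sections.
2. **Attribution.** Keep it as a supplementary, descriptive result. If the full protocol already has attribution judged by assessors blinded to regimen, say so.
3. **Bleeding.** Align the Part B wording with the objectives and the statistical section: major plus clinically relevant non-major bleeding.

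**Cost.** This changes wording in two sections and leaves sample size, treatment and the primary analysis untouched. The article does not say that events judged unrelated are recorded; if the case report form captures only attributed events, it must be widened. Background events will enter the count. If equally common in both arms, they pull a true ratio towards 1 while leaving the risk difference about the same. Open-label reporting bias is reduced, not removed.

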## Study population and patient eligibility

Three-hundred ET patients will be enrolled by 11 Italian hematological centers. Both patients with newly diagnosed and previously diagnosed disease were eligible. Inclusion and exclusion criteria are listed in Table 1. The following characteristics will be recorded at study entry: age at diagnosis; history of thrombosis or major bleeding; mutational profile (i.e., JAK2, CALR, and MPL mutations); blood count; spleen size; constitutional symptoms; and cytoreductive agents. Of note, the study was designed and approved by the AIFA and Ethic Committees before the publication of the revised 2016 WHO classification for tumors of the hematopoietic and lymphoid tissues^38^, therefore the inclusion criteria reflect the WHO classification at the time of study approvals.

**Table 1 Tab1:** Inclusion and exclusion criteria

Main inclusion criteria	Main exclusion criteria
*All of the following*: Age between 18 and 75 years A WHO 2008-defined ET diagnosis Ongoing aspirin 100 mg daily since at least 3 months, according to the judgment of the referring hematologist The patient understands and voluntarily signs an informed consent	*Any of the following*: Platelet count > 1 000 000/μl on three occasions over the 2 months before enrollment Diabetes according to American Diabetes Association criteria Creatinine level > 1.5× upper limit of normal Liver disease defined as AST and/or ALT values > 3× upper limit of normal Active gastrointestinal disease Obesity (BMI > 30 kg/m^2^) Smoking habits (>5 cigarettes/day) History of major bleeding History of cancer in the previous 3 years, except for treated early-stage squamous or basal cell skin carcinomas Pregnancy or lactation Use of nonsteroidal anti-inflammatory drugs >3 times/week Use of antiplatelet agents other than aspirin 100 mg Use of oral anticoagulants including anti-vitamin K, anti-Xa, or -IIa agents Use of heparins or fondaparinux Chronic use of steroids (prednisone > 5 mg/day or equivalent)

Cytoreductive drugs, namely hydroxyurea, pipobroman, busulphan, interferon, and anagrelide will be allowed to control platelet count. Patients will be prescribed proton pump inhibitors according to the Italian regulatory indications. In case of the occasional need of analgesic/antipyretic drugs, patients will be instructed to take paracetamol (up to 2000 mg daily) and to avoid traditional nonsteroidal anti-inflammatory drugs (NSAIDs) known to have a pharmacodynamic interaction with low-dose aspirin that may limit the extent of platelet COX-1 acetylation^21^. Patients will be instructed to take paracetamol for a maximum of 3 days/week, if necessary

## Study end points and statistical analysis

The co-primary end points of part A are as follows: (1) platelet TXA_2_ production ex vivo, as reflected by serum TXB_2_, measured in samples collected in the morning, before the next aspirin intake; and (2) vascular PGI_2_ biosynthesis in vivo, as reflected by urinary PGIM excretion in a urine sample collected in the morning before the next aspirin intake. Urinary TXM excretion represents a secondary end point. These biomarkers will be measured at randomization and at 14 ± 2 days thereafter.

The primary end point of part B is represented by serum TXB_2_ measured 10 times in samples collected in the morning, before the next aspirin intake. The secondary end points are related to exploratory assessment of safety and tolerability of the experimental aspirin dosing regimen, and stability over time of in vivo platelet activation, as detailed above.

Based on previous findings^12,14^, we expect the mean ± standard deviation (SD) serum TXB_2_ in ET patients on aspirin 100 mg od and 100 mg bid to be 22 ± 33 and 5.0 ± 6.0 ng/ml, respectively. We plan to test with *α*-error of 0.05 and a *β*-error of 0.2 (power 80%) the following hypotheses:100 mg bid is superior to 100 mg od, with a ≥50% reduction in serum TXB_2_ (required sample size 70 patients/arm)100 mg tid is superior to 100 mg bid, with a ≥50% reduction in serum TXB_2_ (required sample size 70 patients/arm)

Anticipating a 30% dropout over the entire study duration, we plan to enroll 100 patients/arm to ensure adequate statistical power. For urinary PGIM, we expect the mean ± SD PGIM excretion rate in ET patients on aspirin 100 mg od to be 195 ± 119 pg/mg creatinine^33^. Using the above sample size (*n* = 70 patients/arm), the study has 80% power to test the hypothesis that any experimental treatment may reduce urinary PGIM to <140 pg/mg creatinine, i.e., by >30%. This threshold of PGIM inhibition vs. the standard dosing regimen can be considered reasonably safe based on the following considerations: urinary PGIM excretion is minimally affected by low-dose aspirin in healthy subjects^32,33^; in ET subjects, aspirin 100 mg bid did not significantly modify PGIM as compared to 100 mg od^33^; and this threshold corresponds to the intra-subject coefficient of variation on repeated measurements of PGIM excretion over time^39^.

The same 300 ET patients will be randomized in part B of the study that will test the long-term persistence of superior biochemical efficacy of the optimized vs. standard dosing regimen. In all, 112 patients/arm will be needed to assess with an *α*-error of 0.05 and 80% power, a reduction of at least 50% in serum TXB_2_ with the optimized regimen (100 mg bid or tid) vs. the standard aspirin regimen (100 mg od), in at least 6 out of 10 determinations performed over 20 months.

Differences in mean serum TXB_2_ values will be evaluated by one-way analysis of variance, using Scheffe multiple-comparison test to allow comparisons of the three different treatments in part A. Analysis of covariance using multiple regression with dummies for the different treatments will be used if, at single univariate analysis, major differences (*p* < 0.05) in the distribution of gender, age, platelet count, JAK2 mutational status, spleen size, aspartate aminotransferase, alanine aminotransferase, or creatinine, and type of cytoreductive drug (if any) will be present between the three treatment subgroups. Both intention-to-treat and per-protocol analyses will be carried out.

It can be reasonably anticipated that a portion of the ET patients recruited in this trial according to the 2008 WHO diagnostic criteria^4^ might fall into the category of the pre-PMF according to the revised 2016 WHO criteria^38^. In a large international study of 1104 ET patients, diagnosis was revised to pre-PMF in 16%;^40^ these patients have been reported having an increased tendency toward bleeding^41^. Therefore, we will perform a pre-specified secondary analysis in the group of patients who will develop major and/or non-major clinically relevant bleeding in comparison with the patients with an uneventful course. All the bone marrow biopsies of the recruited patients will be revised by an ad hoc committee formed by the pathologist of the Coordinating Center and the pathologist of the Center where the patient had been recruited in order to assess whether patients had a true-ET or a pre-PMF according to the revised WHO classification;^38^ both the pathologists involved in the bone marrow revision will be blinded to the clinical characteristics of the patients. If the pathologists will provide different opinions, we will consult with a qualified third pathologist. The incidence of pre-PMF in patients with bleeding events will be compared to that found in non-bleeders.

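### Part A's 70 and Part B's 112 patients per arm rest on undisclosed, differing assumptions for a nominally equal target, and Part A's 80% is not the power of the ANOVA with Scheffé comparisons that the protocol names

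*Protocol article*

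**What the plan says.** All the relevant text is in the protocol article, section Study end points and statistical analysis.

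- Expected serum TXB2 (mean ± SD) is given as "100 mg od and 100 mg bid to be 22 ± 33 and 5.0 ± 6.0 ng/ml". No value is given for tid.
- Error rates for Part A: "We plan to test with *α*-error of 0.05 and a *β*-error of 0.2 (power 80%) the following hypotheses". Sidedness is not stated.
- Hypothesis 1: "100 mg bid is superior to 100 mg od, with a ≥50% reduction in serum TXB_2_ (required sample size 70 patients/arm").
- Hypothesis 2: "100 mg tid is superior to 100 mg bid, with a ≥50% reduction in serum TXB_2_ (required sample size 70 patients/arm").
- Part B: "112 patients/arm will be needed to assess with an *α*-error of 0.05 and 80% power, a reduction of at least 50% in serum TXB_2". The comparison there is the regimen chosen after Part A against od, and the criterion must be met at six or more of the ten planned measurements. Again no sidedness and no SD are stated.
- Planned analysis for Part A: one-way analysis of variance on mean serum TXB2, with Scheffé's procedure for comparing the three treatments. Covariance adjustment is added if baseline imbalances appear. No test is named for Part B, and no transformation is mentioned for either part.

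**The concern.** The two parts state nominally the same effect, α and power against the same comparator, yet one needs 70 per arm and the other 112. A reader cannot tell which variance the investigators believe, or whether α is one- or two-sided.

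Part A also names its analysis. An ANOVA with Scheffé comparisons is non-directional, uses a larger critical value than a simple two-sample test, and pools the error variance over all three arms. The printed SDs differ more than fivefold (33 vs 6.0). A two-sample calculation made arm pair by arm pair therefore need not describe the power of that analysis.

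At stake is hypothesis 2 in particular. It compares the two candidate regimens from which Part B's experimental arm is chosen.

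**Working it through.** **1. Reproducing the printed sizes.** Inputs: od 22 ± 33 and bid 5.0 ± 6.0 (printed). A 50% reduction from 22 gives Δ = 11; a 50% reduction from 5.0 gives Δ = 2.5. Formula: n per arm = (z_α + z_power)² × (SD₁² + SD₂²) / Δ², with z_power = 0.842 and z_α = 1.645 (one-sided) or 1.960 (two-sided). The squared sum is 6.18 or 7.85.

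| Contrast | SDs | n, one-sided 5% | n, two-sided 5% | Two-sided power at 70 | Two-sided power at 112 |
|---|---|---|---|---|---|
| 22 vs 11 | 33 / 16.5 | 69.6 → **70** | 88.3 → 89 | 70% | 88% |
| 22 vs 11 | 33 / 33 | 111.3 → **112** | 141.3 → 142 | 51% | 70% |
| 22 vs 11 | 33 / 6 (printed) | 57.5 → 58 | 73.0 → 73 | 78% | 94% |
| 5.0 vs 2.5 | 6 / 6 | 71.2 → 72 | 90.4 → 91 | 69% | – |
| 5.0 vs 2.5 | 6 / 3 | 44.5 → 45 | 56.5 → 57 | 88% | – |

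Example: 6.18 × (33² + 16.5²) / 11² = 6.18 × 1361.25 / 121 ≈ 69.6.

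The exact matches are 70 with 33/16.5 and 112 with 33/33, both one-sided. None of the SD pairs tried gives both figures under one sidedness. The 112 is a single-time-point result, so the 6-of-10 rule contributes nothing to it. Hypothesis 2's 70 is approached, not met exactly, by 6/6 one-sided.

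**2. Power of the named Part A analysis at 70 per arm.** Scheffé's critical value for three groups and 207 error degrees of freedom is c = √(2 × F₀.₉₅(2, 207)) ≈ 2.466, against 1.971 for an unadjusted two-sided t test. The test uses the pooled error SE_p = √(MSE × 2/70), where MSE is the mean of the three variances. The true standard error of a pairwise difference is SE_d = √((SD₁² + SD₂²)/70). Approximately, power = Φ((Δ − c × SE_p) / SE_d).

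*od vs bid, 22 vs 11* (SDs in order od/bid/tid; the tid SD is always an assumption):
- 33/33/33: SE_p = SE_d = 5.578; (11 − 13.75)/5.578 = −0.49; power 31%.
- 33/16.5/8.25: SE_p = 3.690, SE_d = 4.410; (11 − 9.10)/4.410 = 0.43; power about 67%.
- 33/6/3: SE_p = 3.286, SE_d = 4.009; (11 − 8.10)/4.009 = 0.72; power about 76%.

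*od vs bid at the expected 22 vs 5.0* (33/6/3): (17 − 8.10)/4.009 = 2.22; power about 99%.

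*tid vs bid, 5.0 vs 2.5:*
- 33/6/3: SE_d = √(45/70) = 0.802; (2.5 − 8.10)/0.802 = −7.0; power essentially 0%.
- 33/6/6: SE_p = 3.325, SE_d = 1.014; (2.5 − 8.20)/1.014 = −5.6; power essentially 0%.

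The observed difference would have to exceed about 8.1 ng/ml, which is more than the whole expected bid mean of 5.0. A simulation with normal data agrees with these figures to within about one percentage point.

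**3. Log scale.** The printed coefficients of variation are 33/22 = 1.5 and 6.0/5.0 = 1.2. If TXB2 is log-normal, the log variance is ln(1 + CV²): 1.179 and 0.892. A 50% reduction is ln 2 = 0.693. Unadjusted two-sided 5% needs n = 7.85 × (sum of the two log variances)/0.693², which is 29.1 (CVs 1.2/1.2), 33.8 (1.5/1.2) or 38.5 (1.5/1.5) per arm. Power at 70 per arm is 97% to 99%. With c = 2.466 and equal log variances across arms, it is Φ(0.693/√(2.357/70) − 2.466) ≈ 90% at CV 1.5 and Φ(0.693/√(1.784/70) − 2.466) ≈ 97% at CV 1.2.

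**The case against.** The tempting stronger reading is that both sizes can be reached only with a one-sided test, so that the stated power is simply wrong in both parts. The document does not support this, for several reasons.

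- α is given without sidedness and the hypotheses are directional. On a one-sided 5% test with the matching SDs, both 70 and 112 give 80% power.
- For Part A, the printed SDs 33/6 with an unadjusted two-sided test give 78% at 70 per arm, which is close to the claim.
- The protocol names no test for Part B, so the fall to 70% there is conditional on a two-sided α and SD 33/33. With the printed 33/6, two-sided power at 112 is 94%.
- The contrasts are not identical: Part B compares whichever regimen is selected, over repeated determinations.
- A condensed article may leave sidedness and the SD for each calculation to the full protocol.
- The 70 assumes that the full 30% dropout has already occurred. That rate covers the entire study, and Part A lasts two weeks.

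Most of this stands, and it limits the point for Part B to undisclosed and inconsistent inputs. It does not rescue Part A, where the article itself fixes the analysis. Even with 100 per arm (c ≈ 2.460), the od-bid power for 22 vs 11 runs from Φ((11 − 2.460 × 4.667)/4.667) ≈ 46% with SD 33 throughout to Φ((11 − 2.460 × 2.749)/3.354) ≈ 90% with 33/6/3. For tid vs bid it remains near zero: (2.5 − 6.76)/0.671 = −6.3.

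It is also fair to say that the od-bid comparison is in little danger if the expected 22 vs 5.0 is right.

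**Conclusion.** The point holds in two separate parts.

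**Part A: the stated 80% is not the power of the named analysis.** At 70 per arm on raw TXB2, a 50% od-bid reduction has about 31% to 76% power, depending on the SDs. Tid vs bid at 5.0 vs 2.5 has essentially none (tid SD assumed to be 3 or 6). The hypothesis 2 result is the more serious: it does not depend on sidedness and follows from pooling an od SD of 33 into a comparison of two low-variance arms.

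**Part B: the basis is undisclosed and inconsistent with Part A.** It is not shown to be wrong. Power at 112 per arm is 80% one-sided or 70% two-sided with SD 33/33, and 94% two-sided with 33/6. How the 6-of-10 criterion entered the calculation, if at all, cannot be seen.

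The Part A figures assume normal data, an untransformed analysis and the standard pooled-error Scheffé procedure. Since each printed SD exceeds its mean, the data will be skewed, so the raw-scale figures are approximate. That the SD pairs 33/16.5 and 33/33 were the ones used is an inference from the numerical match, not something the document says.

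**What to change.** In Study end points and statistical analysis, state one sidedness for α and one set of SDs, including the value assumed for tid, and use them for both parts. Then take one of two routes.

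1. Keep the raw scale and restate Part A power for the ANOVA with Scheffé comparisons, acknowledging that hypothesis 2 cannot be tested usefully that way.
2. Specify the analysis and the power on log TXB2. There a 50% reduction needs about 29 to 39 per arm with an unadjusted two-sided 5% test (97% to 99% power at 70), and the Scheffé adjustment is then added. This route is preferable because it suits a percentage effect and stops the od variance dominating the tid-bid comparison.

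For Part B, name the test and say how the 6-of-10 criterion enters the calculation of 112.

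The cost is recalculated figures and a few sentences in two paragraphs. Route 2 also changes the analysis scale, which should be fixed before the Part A data are analysed. Enrolment does not change.
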